### 2.4 Interventions

All participants will be randomly assigned to the experimental group that will receive intermittent theta burst stimulation to cerebellar vermis, or control group that will receive false stimulation to cerebellar vermis. We will used a iTBS stimulator(CCY-I type, YIRUIDE GROUP, China) and an “8” coil with an inner diameter of 70 mm. The stimulation plan will follow the safety guidelines and recommendations approved by the International Congress of Clinical Neurophysiology. Stimulation intensity will be 80% of active motor threshold. If the participants can not tolerate the preset intensity, the stimulus intensity will be adjusted to the maximum intensity that the participants can tolerate. The stimulation target is cerebellar vermis that located 1 cm below the external occipital protuberance. The parameters of iTBS were 80% of the resting motor threshold and 50 Hz pulses. The resting motor threshold will be determined as the lowest intensity of stimulation that elicited a motor-evoked potential of at least 50 μV in the relaxed first dorsal interosseus muscle in a minimum of 5 of 10 trials. As shown in Fig 3, iTBS will use intermittent θ rhythm burst stimulation and the parameters will include triplet 50 Hz bursts, repeated at 5 Hz for 2 seconds on and 8 seconds off for a total of 600 pulses per session and 200 seconds. In the experimental group, the “8” coil will be tangent to the scalp of the stimulation site, and the cerebral cortex can cut the magnetic field to generate induced current for true stimulation. In the control group, the “8” coil will be perpendicular to the scalp of the stimulation site, and the cerebral cortex can not cut the magnetic field, which does not generate induced current and can not achieve the stimulation effect.

**Fig 3 pone.0339030.g003:**
[figure not shown]
The stimulation mode of iTBS. The iTBS mode will include 600 pulses, 3 pulses per bundle, with an intra bundle frequency of 50 Hz, stimulation of 0.04s, interval of 0.16s, inter bundle frequency of 5 Hz, continuous stimulation of 10 bundles, interval of 8s, and a total stimulation duration of 200s.

Participants in both groups will receive motor training for balance function. Professional physical therapists will design motor training programs for frail older people with balance dysfunction based on frequency, intensity, time, type, volume, and progression (FITT-VP) principles. The motor training will include muscle strength training, aerobic training, balance training, sensory training, flexibility training, and gait training. Each motor training will be conducted after the iTBS once a day. The training duration will be 30–60 minutes each time, for a total of 20 sessions.

#### 2.5.1 Demographic data (T0).

Participants’ demographic data will be collected at baseline, including sex, age, educational level, nation, marital status, residence, monthly income per capita of family, duration of balance dysfunction, medication, smoking, drinking, chronic disease and main caregivers.

#### 2.5.2 Balance function (T0, T1, and T2).

The Berg Balance Scale, developed in 1989 by Katherine Berg [27], will be used to evaluate balance function. This scale consists of 14 items, such as sitting alone, standing alone, transferring, turning around and picking up. It adopts Likert 4-point rating system and each item is scored from 0 (unable to complete) to 4 (completed). The total score ranges from 0 to 56, and and a higher total score indicates better balance function. The Cronbach’s α of this scale is 0.83 [28].

#### 2.5.3 Frailty (T0, T1, and T2).

The Tilburg Frailty Indicator developed by Gobbens et al. [29] will be used to evaluated frailty level. This scale has three frailty domains, including physical frailty, psychological frailty, and social frailty. It has 15 items and each item is scored using binary classification, with 1 point for “yes” and 0 point for “no”. The total score ranges from 0 to 15. A total score of 5 or above is considered frailty. A higher total score indicates more severe frailty. The Cronbach’s α of this scale is 0.73 [30].

#### 2.5.4 Walking ability (T0, T1, and T2).

Timed-Up and Go Test (TUG test), as a rapid method, was developed by Mathias et al. [31] to measure balance problems. In this study, TUG test will be used to test participants’ walking ability. The steps are: standing up from the chair; walking forward 3 meters at normal pace; turning around; walking back to the chair at normal pace; and sitting down again. The time required to complete the entire process will be recorded. The shorter the time, the better the functional walking ability.

#### 2.5.5 Sensory organisation test, limits of stability and rhythmic weight shift (T0, T1, and T2).

Balance Master system will be used to assess participants’ sensory organisation test, limits of stability and rhythmic weight shift [32]. This system was developed by Guangzhou vedo health & science co., ltd. Balance Master include Balance Manager software, a force platform, pedal, medical grade isolated power supply, a computer with Windows 7, and a color display.

Sensory organisation test can evaluate posture control during different sensory, visual, and vestibular feedback disturbances [32]. During the testing process, inaccurate interference information will be transmitted to the patient’s eyes, feet, and joints, and will be controlled through calibrated support surfaces and/or visual environment swing references. The participant is required to maintain balance to keep their centre of gravity as steady as possible. During the sensory organisation test, each trial will last for 20 seconds and will be repeated three times [33,34].

When testing the limits of stability, a real-time display of the centre of gravity position and stability limit of participants relative to the target placed at the center of the support base will be shown. Once the command is issued, participants must accurately move their centre of gravity from the center position to one of the eight targets as soon as possible (up to 8 seconds), including forwards, forwards-right, right, backwards-right, backwards, backwards-left, left and forwards-left [35].

The rhythmic weight shift will be used to evaluate participants’ ability to perform rhythmic movements of their centre of gravity from left to right (lateral) and forwards to backwards (anterior/posterior) between two targets at three different speeds (slow, medium and fast) [32]. Motion speed and direction control for each direction and speed will be measured.

### 2.6 Statistical analysis plan

We will use IBM SPSS Statistics 23 to analyze the data. P‒P diagram will be used to test the normality of the distribution of measurement data. Mean and standard deviation will be used to describe normally distributed measurement data. The independent sample t-test and a paired-sample t-test will be used for comparisons. Ranking data and non normally distributed measurement data will be described by using the median and interquartile ranges. The Mann‒Whitney U test and Wilcoxon signed rank sum test will be used for comparisons. If the sample characteristics are different in baseline, subgroup analysis will be used. We will divide the participants into different subgroups based on certain characteristics, such as age, gender and educational level, and then analysis will be conducted within each subgroup. Counting data will be described by using number and percentage. Fisher’s exact test will be used for comparisons. Repeated measures analysis of variance (group * time) will be to examine the changes in all repeated measurement outcomes. If the baseline indicators are not comparable, an adjustment to the efficacy contrast of variables will be required. The intention-to-treat principle was used as the analytical strategy for outcome evaluation. *P* < 0.05 indicates statistical significance. All tests are 2-sided.

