### 2.2 Sample size

G Power software (version 3.1.9.2) will be used to calculate the sample size. The balance function measured by the Berg Balance Scale will be the primary outcome. According to a previous study on stroke patients [23], the estimated effect size is 0.380. Alpha is 0.05 (bilateral) and Beta is 0.10. Correlation between repeated measurements is 0.5 and non spherical correction is 1. The total sample size is calculated to be 40. Considering dropout and loss to follow-up, the total sample size is increased by 20%, and the final total sample size is 48.

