### 2.3 Randomization, allocation concealment and blinding

A 1:1 random number sequence will be generated based on a computer. After assessment at baseline, a research assistant will randomly assign eligible participants to one of two groups at a 1:1 ratio after the initial evaluation. The research assistant will place the randomized grouping schemes into some sequentially encoded, sealed, and opaque envelopes. All envelopes will be neatly stored in the locked filing cabinet of the research center in order of their entry numbers. The keys will be kept by the department secretary, who will not participate in any intervention. After evaluating the eligibility of participants and obtaining informed consent, the researchers will request the department secretary to open the envelopes in the order of enrollment to determine participants’ group. The researchers can not be blinded to the assigned interventions. Participants will be blinded to the allocation. Participants will only know that they will receive intervention when entering the group, but they will not know whether it is a real stimulus or a fake stimulus. The two intervention processes will be completely identical in operation. The data collector and statisticians will be blinded to the allocation. The data collector will only record the participant’s enrollment number during the evaluation and will not access any information related to the group. During the data entry and statistical analysis phase, the statisticians will only receive de-identified data labeled with group numbers.

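### The subgroup and adjustment rules depend on observed baseline differences; adjusting the Berg Balance Scale for its baseline in every case would be cleaner and more precise, with no extra participants

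*Protocol article*

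**What the plan says.** Section 2.6 contains two rules that depend on what the baseline data show.

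- Subgroups: "If the sample characteristics are different in baseline, subgroup analysis will be used". Age, gender and educational level are given as examples, and the analysis is then run within each subgroup.
- Adjustment: "If the baseline indicators are not comparable, an adjustment to the efficacy contrast of variables will be required".

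The section does not say when characteristics count as different or indicators as not comparable. It names no covariate or adjustment model, does not say how subgroup results would be combined, and does not say which rule applies if both are triggered.

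The same section prescribes, without condition, a repeated measures ANOVA (group by time) for all repeated outcomes, alongside t-tests or rank tests. The Berg Balance Scale, the primary outcome, is measured at T0, T1 and T2 (section 2.5.2), so its baseline value is one level of the time factor. No default analysis uses baseline as a covariate.

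**The concern.** Allocation is random (section 2.3: "A 1:1 random number sequence will be generated based on a computer"), so baseline differences between arms are chance differences. A rule that reacts to them makes the analysis depend on the data, and without a criterion two analysts could follow section 2.6 and report different results.

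The two rules fail in different ways. The subgroup rule does not do what it seems meant to do: a treatment effect estimated separately in men and in women leaves the overall estimate as unbalanced as before. It also adds tests on fractions of a 48-person trial, each at 0.05. The adjustment rule does correct an imbalance when it is used, but it restricts the more precise analysis to the trials in which an imbalance happens to be noticed. The baseline Berg score is collected from everyone, so that gain is available every time.

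**Working it through.** **Inputs from the protocol article.** Section 2.2: "Alpha is 0.05 (bilateral) and Beta is 0.10"; "the estimated effect size is 0.380"; "Correlation between repeated measurements is 0.5 and non spherical correction is 1"; "The total sample size is calculated to be 40"; "the total sample size is increased by 20%, and the final total sample size is 48". With 1:1 allocation this is 20 per arm before the dropout allowance and 24 per arm in the final sample. Section 2.5.1 lists 13 demographic items.

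**Plan's own figure.** 40 × 1.20 = 48 reproduces. The 40 does not follow at 90% power from the standard repeated-measures calculations tried with f = 0.38 and correlation 0.5 (between-group effect: 58 with two times, 52 with three; interaction: 22 and 18). The article does not name the test used. That is a separate matter, and nothing below depends on it.

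**Assumptions.** The metric of 0.380 is not stated. Read as Cohen's f for two groups, d = 2 × 0.38 = 0.76. Read as d, it stays 0.38. Both are shown.

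**1. How often chance alone triggers a rule.** The plan sets no threshold; a 0.05 test per item is assumed. For k independent items the chance of at least one difference is 1 − 0.95^k.
- Three named factors: 1 − 0.95³ = 14%.
- All 13 items: 1 − 0.95¹³ = 49%.
- Fisher's exact test, which section 2.6 assigns to counts, is conservative here. For a binary item with 20–24 per arm and prevalence 0.1–0.5, its true size is about 1.2–2.9%. At 2.5% per item, 13 items give 1 − 0.975¹³ = 28%.

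**2. False positives from subgroup tests.** With no treatment effect and independent tests at 0.05:
- two tests: 1 − 0.95² = 10%;
- six tests (for example three factors, two levels each): 1 − 0.95⁶ = 26%. The same people appear under each factor, so these tests are not truly independent and 26% is approximate.

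**3. Efficiency of covariate adjustment against the default.** With one baseline and one follow-up, the group-by-time test is the change-score test. Relative to the variance of a single score, the error variance is 2(1 − ρ) for the change score and 1 − ρ² for ANCOVA. At ρ = 0.5 these are 1.0 and 0.75, a 25% reduction.

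Two-sided noncentral-t power at 24 per arm:

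| d | ρ | Change score | ANCOVA |
|---|---|---|---|
| 0.76 | 0.3 | 59% | 77% |
| 0.76 | 0.5 | 73% | 84–85% |
| 0.76 | 0.7 | 91% | 95% |
| 0.38 | 0.5 | 25% | 32% |

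The formula gives 84.5% for ANCOVA at d = 0.76 and ρ = 0.5; a simulation of 40,000 trials gives 83.7%. At 20 per arm with d = 0.76 and ρ = 0.5, power is 65% against 77%.

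**4. Adjusting only after a significant baseline test.** The same simulation (ρ = 0.5, d = 0.76, baseline Berg score tested at 0.05) gives power of 66% at 20 per arm and 74% at 24 per arm. Always adjusting gives 77% and 84%. With no treatment effect, the conditional rule has an overall type I error of 4.2–4.4%. Among the trials with a significant baseline difference, the unadjusted analyses reject in 17–20% and ANCOVA in about 5%.

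**The case against.** Four replies have force.

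- *The adjustment rule works when it is used.* This stands. Once triggered, the plan requires it, so it is not optional, and it corrects the imbalance. A reader might infer that the rule inflates the false-positive rate; step 4 shows that it does not. Its faults are the missing criterion and the lost precision.
- *Subgroups are additional.* A reader might infer that the subgroup analyses replace the whole-sample comparison, and so compare power of about 43% at 12 per arm with 73% at 24 per arm (d = 0.76). Section 2.6 never says this: the group-by-time ANOVA is prescribed unconditionally. That comparison is therefore no measure of the loss. What stands is that the added analyses do not repair an imbalance and do add tests.
- *Baseline is already used.* A reader might infer that the default ignores the baseline Berg score. It does not, because T0 is a level of the time factor. The difference is one of efficiency, and it narrows as the correlation rises: from 91% to 95% at ρ = 0.7.
- *The 49% is close to an upper figure.* This also stands. It needs all 13 items tested independently at a full 5%, which the plan does not say.

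Covariate detail could properly sit in an analysis plan that is not shown. That does not answer the point, because the two conditional rules are written in the protocol article itself.

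**Conclusion.** The point holds in a limited form. Section 2.6 ties the analysis to observed baseline differences without a criterion, and its subgroup rule cannot remove an imbalance from the overall estimate. The primary comparison is not invalidated, since the unconditional whole-sample analysis remains. This is an improvement that needs no extra participants and should be made, rather than a flaw that defeats the trial.

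Its size depends on two quantities. At the protocol's correlation of 0.5, always adjusting cuts error variance by 25% against the change-score equivalent of the default. At 24 per arm this adds 11 to 12 percentage points of power if 0.380 is Cohen's f, and about 7 points if it is d. With d = 0.76 the gain is about 18 points at correlation 0.3 and under 4 at 0.7. These figures treat the trial as having two time points; the three-time ANOVA would differ in detail. The case against data-triggered rules depends on neither the effect size nor the correlation.

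**What to change.** Before outcome data are examined, amend section 2.6 as follows.

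- Delete both conditional rules.
- State that the Berg Balance Scale comparison is always adjusted for baseline Berg score, whatever the baseline table shows: by ANCOVA, or by a repeated-measures model of T1 and T2 with baseline Berg score as covariate.
- Adjust each continuous secondary outcome for its own baseline in the same way.
- Present baseline characteristics by arm descriptively, without letting any difference change the analysis.
- Keep any age, sex or education subgroups as exploratory treatment-by-subgroup interactions.

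The cost is one degree of freedom in each model and a change of analysis wording. No additional participants, visits or measurements are needed.

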## 3. Discussion

Frailty is an age-associated biological syndrome. With the advent of global aging, the number of frail older people is increasing and the prevalence of frailty in people older than 65 years is high [36,37]. Frailty is the main risk factor for disability [38,39]. Frail older patients frequently experience a decline in muscle strength, gait speed and balance, which ultimately leads to the loss of independence in daily activities and falls [40,41]. Therefore, it is important to improve balance function in frail older people.

It is crucial that frailty is reversible, and timely rehabilitation intervention for older people with frailty can help improve their frailty level and alleviate the adverse reactions caused by frailty. This paper outlines a protocol for the evaluation of iTBS to cerebellar vermis on balance function in frail older people with balance dysfunction. The outcomes of this randomized controlled trial will be used to provide information for clinical decision-making.

This study trials an iTBS intervention, which specifically targets cerebellar vermis that receive little attention. To the authors’ knowledge, this is the first study to examine the effects of iTBS to cerebellar vermis on balance function in frail older people. Therefore, this study represents an important contribution to the evidence base for rehabilitation intervention targeted to this underserved population. iTBS can simulate the burst discharge pattern of physiological action potentials in the central nervous system, such as the common 5 Hz cluster and bundle action potential patterns in the hippocampus [42]. It has the advantages of short stimulation time, low stimulation intensity, long action time, and being closer to the physiological state of neural activity [43], making it easier to induce neural plasticity [44]. In addition, maintaining balance depends on the complex coordination and integration of multiple systems within the body [45]. According to a fMRI research, the cerebellar vermis is strongly connected with the visual network [46]. It is also suggested that the cerebellar vermis can coordinate eye and body movements, and provide balance-related visual and auditory input [13]. Therefore, based on previous evidence, we believe that this protocol will guide the development of a meaningful clinical study and the findings will be valuable.

However, the study also has some limitations. First, this is a single-center trial. So, the findings can not represent the entire population. After completing the trial in one center, we will consider conducting multi-center validation. Moreover, it is unknown whether this research plan is accepted by the participants. So, we will conduct a feasibility trial according to this protocol to make sure the progress of the formal trial.

In conclusion, this study aims to provide a randomized controlled trial protocol, to evaluate the efficacy of intermittent theta burst stimulation to cerebellar vermis on balance function in frail older people. It may provide more rehabilitation support to frail older people with balance dysfunction and promote the realization of healthy aging.
